### Data collection

At baseline, the in-charge nurse will distribute the questionnaires to participants or their family caregiver. They will complete the questionnaires once the consent form is signed and before the individualized discharge education is provided. The patient’s in-charge nurses at the hospital will provide assistance to participants should they have any questions about the questionnaire. Clinical outcomes (BP, HbA1c and lipid values) will be directly recorded from the health record of patients by a research assistant.

At 3-month and 6-month follow-up, community nurses will distribute the questionnaires to participants in the intervention group when they visit the community health service center. Community nurses will be available to assist patients should they have any questions about the questionnaire. In the usual care group, a nurse in the medical specialist clinics will distribute the questionnaire to participants when they visit the outpatient clinic at 3-month and 6-month follow-up. The nurse will be available to assist patients should they have any questions.

Completed questionnaires will be placed in a prepared sealable envelope to maintain confidentiality. The researcher will prepare a drop box in each ward, community health service center and outpatient clinic. Participants will return the sealed questionnaires to the drop box. The research assistants will collect completed questionnaires on a weekly basis.

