
#### Stage 2: regular follow-up interventions over 6 months at community health service centers

2.1.Fortnightly telephone call.Patients will receive a fortnightly telephone call at home from the community nurse to monitor their progress toward setting goals and medication adherence.2.2.Monthly community health service center visit.Patients will be asked to visit the community nurse and GP at the community health service center every month for follow-up visits.2.2.1.Patients will receive blood pressure measurement every month by the community nurse.2.2.2.Patients will receive a review and assessment from the community nurse on their adherence to medication and lifestyle recommendations, and their progress toward lifestyle modification goals.2.2.3.Patients will receive reinforced health education from the community nurse to improve their self-management ability and treatment adherence. Patient will be given health education on preventing or treating geriatric conditions based on the “Fulmer SPICES Comprehensive Assessment Tool for Older Adults”.2.2.4.Patients will receive an assessment from the GP on their clinical outcomes, problems of nonadherence to medication, medication side effects, drug therapy problems, drug-related needs and clinical events occurred.2.2.5.Patients will be asked to discuss their individualized treatment plan and medication adjustment with the GP.2.2.6.Patients will be asked to document their medication changes in the “intervention diary—patient version”.2.2.7.Patients will be reminded of the categories, dosage and frequency of medication required to be taken prior to the next visit by community nurse.2.3.GP and medical specialist collaboration.The GP will discuss with the medical specialist at the hospital via email or telephone when necessary to adjust medication. BP, HbA1c and lipid readings will be recorded by the community nurses and formatted as a monthly report and then sent to medical specialists for review. Urgent symptoms will be communicated to the medical specialist immediately for additional orders by the GP.

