#### Secondary outcomes

Secondary outcomes are the following outcomes at 6-month follow-up adjusted for baseline value: (1) hypertension and diabetes-related health knowledge score measured by a combination of the Hypertension Knowledge-Level Scale (HK-LS) [32] and the Diabetes Knowledge Questionnaire (DKQ) [33]; (2) medication adherence and health lifestyle adherence score measured by the Treatment Adherence Questionnaire of Patients with Hypertension (TAQPH) [34]; (3) HbA1c and lipid values; (4) quality of life score measured by the hypertension scale of the Quality of Life Instruments for Chronic Diseases (QLICD-HY) [35]; (5) the incidence of adverse events and complications associated with hypertension, diabetes, treatments and geriatric syndromes recorded by patients/or carers in the “intervention diary—patient version”; and (6) the incidence of unplanned hospital admissions/use of emergency care services due to uncontrolled hypertension, diabetes and geriatric syndromes recorded by patients or carers in the “intervention diary—patient version”.

Through the study, we hope to identify the challenges that patients face in their hypertension management in the community healthcare settings and to evaluate how to overcome these challenges by improving the capacity of the primary care system. Hence, two open-ended questions will be included for patients upon study completion: (1) Are you satisfied with the follow-up provided by the GP and community nurse in the community health service center? (If not, please explain the reason); and (2) Did you encounter any difficulties of care in the community health service center after discharge? (If yes, please list the difficulties you encountered).

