### Quality control procedures

Quality of data collection will be ensured during the whole study phases. Two 1-h workshops and ongoing support at each participating site will be provided to the health professionals to allow them to discuss, understand and follow the study protocol. Research assistants will be employed to distribute and collect the questionnaires. Consent forms, questionnaires and other data collection documents will be checked for completeness. Data at three time points (baseline, 3-month and 6-month follow-up) will be checked using the birth date of patients to ensure the data are matched correctly. The quality of the study will be overseen by the PhD supervision team and the representative of the Department of Scientific Research Management at Health and Family Planning Commission of Jiangxi Province, China. The data entered into SPSS will be checked to prevent input errors by the other two PhD fellows who are not involved in this study. The compliance of patients with the interventions will be optimized by a telephone call from the nurse at the community service center to remind them of the follow-up visits at the community health service center.

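### At 3 and 6 months the role that delivers the education and adherence coaching also hands out, and is on hand for questions about, the knowledge, adherence and quality-of-life questionnaires in the intervention arm only, while another section gives distribution to research assistants

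*Protocol article*

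**What the plan says.** Data collection in the protocol article covers the 3- and 6-month questionnaires by arm. In the intervention arm, "community nurses will distribute the questionnaires to participants in the intervention group when they visit the community health service center", and "Community nurses will be available to assist patients should they have any questions about the questionnaire". In usual care, "a nurse in the medical specialist clinics will distribute the questionnaire to participants when they visit the outpatient clinic", and that nurse is likewise available for questions. Completed forms go into a sealable envelope and a drop box. In this section the only questionnaire task of the research assistants is weekly collection.

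The description of Stage 2 gives the community nurse the main follow-up work of the intervention: "Patients will receive a fortnightly telephone call at home from the community nurse to monitor their progress toward setting goals and medication adherence", and, at the monthly visit, a review of adherence and further teaching: "Patients will receive reinforced health education from the community nurse to improve their self-management ability and treatment adherence".

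Secondary outcomes lists the scores that come from these forms: knowledge (HK-LS and DKQ), medication and lifestyle adherence (TAQPH) and quality of life (QLICD-HY).

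Quality control procedures names different people as distributors: "Research assistants will be employed to distribute and collect the questionnaires".

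**The concern.** There are two linked problems.

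First, the article names two different distributors. A site following Data collection uses nurses; a site following Quality control procedures uses research assistants. Three secondary outcomes depend on how these forms are administered.

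Second, if Data collection is followed, the arms differ in who stands beside the patient. An intervention patient answers a knowledge test with a question-answerer from the role that taught the material, and an adherence scale in front of the role that has been monitoring adherence. On a knowledge item, an explanation can turn into a prompt. On an adherence item, the patient may give the answer that the coach hopes for. A usual-care patient meets neither situation. Any resulting shift would be mixed with the treatment effect and could not be separated from it in the analysis.

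**Working it through.** **Text comparison**

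| Question | Intervention arm, 3 and 6 months | Usual care, 3 and 6 months |
|---|---|---|
| Who hands out the forms (Data collection) | Community nurse | Specialist-clinic nurse |
| Who is available for questions (Data collection) | Community nurse | The same clinic nurse |
| Does that role deliver the intervention? | Yes: teaching, calls, adherence review (Stage 2) | None described |
| Who hands out the forms (Quality control procedures) | Research assistants | Research assistants |

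The first and last rows cannot both be carried out as worded. The third row is the asymmetry: help is available in both arms, but only in one does it come from the intervention role.

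**Do the stated safeguards remove it?**
- The envelope and drop box protect answers after completion, not while the form is being filled in.
- Blinding and allocation concealment blinds the statistician, who cannot undo a shift already in the data. The same section says that those delivering the intervention know the allocation.
- Adjustment for baseline does not help, because the difference arises at follow-up. Baseline forms are completed before the discharge education, and no difference between arms is described at that point.
- The limitations in the Discussion mention bias in patients' self-report under open-label conditions, but not the nurses' double role.

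**Illustration of size**

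The article gives no figure for this bias, so there is none to reproduce. Inputs from Sample size: 5 wards per arm, 25 completers per ward (125 per arm), ICC 0.05. Assumptions not in the article: the blood-pressure ICC applies to the questionnaire scores; the administration shift is 0.1, 0.2 or 0.3 SD; there is no true effect; the comparison uses 10 − 2 = 8 degrees of freedom without gain from covariates.

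1. Variance inflation: 1 + (25 − 1) × 0.05 = 2.20. (The design effect of 1.48 in the article is the square root of 2.20, so it is on the standard-deviation scale; the variance needs 2.20.)
2. Standard error of the difference: √(2 × 2.20 / 125) = 0.188 SD.
3. Two-sided 5% critical value of t on 8 df: 2.306.
4. Noncentrality = shift / 0.188: 0.53, 1.07 and 1.60.
5. P(|t| > 2.306) under the noncentral t on 8 df:

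| Assumed shift | ICC 0.05 | ICC 0.01 (assumed) | ICC 0.10 (assumed) |
|---|---|---|---|
| 0 | 5% | 5% | 5% |
| 0.1 SD | 7.6% | 9.6% | 6.7% |
| 0.2 SD | 15.6% | 24.1% | 11.8% |
| 0.3 SD | 29.2% | 46.6% | 20.6% |

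The two outer columns repeat steps 1 to 5 with variance inflation 1.24 and 3.40 (standard errors 0.141 and 0.233 SD). The table shows how sensitive the test would be to a shift. It is not evidence that one occurs.

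**The case against.** The strongest reply is that the arms are deliberately parallel. A nurse hands out the form in each arm and is available for questions in each arm, the nurse acts only if asked, and the sealed envelope keeps the finished answers private. The sentence in Quality control procedures can be read as a loose summary, with research assistants supplying and collecting the forms and nurses passing them to patients. The article already flags self-reported outcomes as open to bias.

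Much of this stands, and it rules out several stronger readings that a reader might infer:
- *Help exists in one arm only.* It does not; usual care has the same provision. Only help from the intervention role is one-sided.
- *Nurses fill in the forms.* The text has them available for questions and nothing more.
- *The same individual teaches and administers.* The text identifies a role. It describes no separation, but does not say that it is one person.
- *Baseline is biased too.* The in-charge nurse's part at baseline also conflicts with Quality control procedures, but it precedes the education and is not shown to differ by arm.
- *The main result is compromised.* The primary outcome does not come from these questionnaires.
- *Scores will be pushed upward.* The direction is plausible, but neither the existence nor the size of a shift is established.

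What does not stand is the parallel itself: the two nurses hold different positions towards the patient, and that is the feature at issue. The loose-summary reading is possible, but it needs the reader to supply a division of labour that the article does not state. The admitted limitation concerns patients' knowledge of their allocation, which is hard to avoid; the administrator's double role can be avoided.

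**Conclusion.** The point holds in a limited form. The two sections conflict on who distributes the questionnaires. If Data collection is followed, three questionnaire-based secondary outcomes (knowledge, adherence, quality of life) are collected at 3 and 6 months under conditions that differ by arm and may favour the intervention. The size is unknown. The range of about 8% to 29% false positives rests on assumed shifts of 0.1 to 0.3 SD and on an ICC borrowed from blood pressure; a smaller ICC would make the rates higher and a larger one lower. The conclusion rests on the text and not on these figures. Because only secondary outcomes are affected, this is a change that should be made, not a threat to the primary analysis.

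**What to change.** Reconcile Data collection with Quality control procedures, and use one arrangement in both arms at 3 and 6 months:
- Research assistants distribute the questionnaires and handle queries, in person or by telephone.
- Queries are answered from a fixed script that covers how to use the form and excludes help with content.
- Where a nurse has to hand over the form, that nurse gives no help with answers.
- The sealed envelope and drop box stay.
- Align the baseline wording with the same statement of who distributes, for consistency only.

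The cost is wording, scheduling and some research assistant time at follow-up visits in six community centers and the hospital outpatient clinics. The article already says that research assistants are employed to distribute the forms, but gives neither their number nor their hours, so it cannot be assumed that they could attend every visit without added staff. Telephone support with the script is the cheaper route. If nothing else is changed, the limitations should name the nurses' double role.

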### Quality control procedures

Quality of data collection will be ensured during the whole study phases. Two 1-h workshops and ongoing support at each participating site will be provided to the health professionals to allow them to discuss, understand and follow the study protocol. Research assistants will be employed to distribute and collect the questionnaires. Consent forms, questionnaires and other data collection documents will be checked for completeness. Data at three time points (baseline, 3-month and 6-month follow-up) will be checked using the birth date of patients to ensure the data are matched correctly. The quality of the study will be overseen by the PhD supervision team and the representative of the Department of Scientific Research Management at Health and Family Planning Commission of Jiangxi Province, China. The data entered into SPSS will be checked to prevent input errors by the other two PhD fellows who are not involved in this study. The compliance of patients with the interventions will be optimized by a telephone call from the nurse at the community service center to remind them of the follow-up visits at the community health service center.

### Blinding and allocation concealment

Participants will not know their group allocation during the recruitment and baseline data collection. The research recruiter who is blinded to the group allocation and has no interest in the study will assist the recruitment of participants. Allocation will be disclosed to participants after the baseline data collection. Due to the nature of the study interventions, health professionals who deliver the intervention will know the group allocation during the trial. However, the statistician involved in the data analysis is blinded to the group allocation.

### Intervention fidelity

Intervention fidelity refers to the extent that proposed interventions are delivered as planned in the protocol. The items of interventions recorded by both patients and community health professionals include: (1) intervention diary—patient version; and (2) intervention record—community nurse and GP version. Compliance with required interventions will be matched using these two tools.

### Dealing with contingencies

Possible contingencies are the following: (1) patients refuse to participate in the project; the strategy to deal with this will be to extend the recruitment period to gain sufficient sample size; and (2) unexpected tasks that health services need to deal with, such as outbreak of infectious disease; the strategy to deal with this will be to temporarily cease the trial and recommence when the health service returns to normal. The Department of Scientific Research Management at Health and Family Planning Commission of Jiangxi Province, China, will deal with the contingencies that may occur during the study.

### Statistical methods

Statistical analysis will be performed using Statistical Package for Social Science (SPSS) version 23 and STATA software version 14. To test the effectiveness of the intervention on the primary and secondary outcomes, a multivariate multilevel mixed-effects linear regression model will be used to analyze outcomes. This is due to the hierarchical structure of the data and is based on the consideration of the correlations between participants’ repeated measurements over time. Because the participants are nested within hospital wards, we will fit a three-level mixed model with random intercepts at both the cluster and the participant-within-cluster levels. Thus, models will account for the clustering in wards, participants within clusters and over time using the *mixed* command. Wards and participants within wards will be treated as random effects. The main effects will be group (intervention or comparison), time (baseline, 3 and 6 months) and group × time interaction. A small-sample correction to the restricted maximum likelihood estimator will be used to improve the inference for the fixed parameters and is available in STATA *mixed* command. Models will be adjusted by baseline value and confounders that include age, gender, body mass index (BMI), duration of hypertension, duration of diabetes, smoking status and education level [37, 38]. A univariate model will also be used for unadjusted estimates. The level of significance will be set at *p* < 0.05. Where appropriate, 95% confidence intervals (95% CIs) will be reported along with *p* values.

Data analysis will be performed according to the intention-to-treat principle. Participants who withdraw or do not complete the 6-month follow-up will be included in the analysis. A multiple imputation technique will be used for large missing data.

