**Methods:**

A cluster randomized controlled trial will randomly allocate 10 wards from four hospitals in Nanchang to either an intervention group (*N* = 5) or a usual care group (*N* = 5). At least 27 participants will be recruited from each ward and the estimated sample size will be 135 patients in each group. The intervention includes individualized self-care education prior to discharge and 6-month follow-up in community health service centers. Health professionals from both hospitals and community health service centers will be resourced to collaborate on the implementation of the postdischarge interventions that reinforce self-care. The primary outcome is systolic blood pressure at 6-month follow-up adjusted for baseline value. Secondary outcomes are self-care knowledge, treatment adherence, HbA1c and lipid levels, quality of life, the incidence of adverse events and the incidence of unplanned hospital readmission at 6-month follow-up adjusted for baseline value. A multilevel mixed-effect linear regression model will be used to compare the changes in health outcomes between the intervention and usual care groups.

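### The linear model with baseline row and baseline covariate cannot be run as written for adverse events and unplanned admissions, which the text describes only as follow-up events

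*Protocol article*

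**What the plan says.** The Statistical methods section sets one model for the primary and secondary outcomes alike: "a multivariate multilevel mixed-effects linear regression model will be used to analyze outcomes". It is fitted in Stata, where "models will account for the clustering in wards, participants within clusters and over time using the *mixed* command"; that command fits a Gaussian linear mixed model. The fixed part is given as "The main effects will be group (intervention or comparison), time (baseline, 3 and 6 months) and group × time interaction", and the models are further adjusted for the baseline value and a list of patient characteristics. No outcome is exempted, and no logistic, Poisson or other generalised model is named.

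The outcome definitions repeat the baseline adjustment. The Secondary outcomes section opens with "Secondary outcomes are the following outcomes at 6-month follow-up adjusted for baseline value" and then lists six items. Item (5) is "the incidence of adverse events and complications associated with hypertension, diabetes, treatments and geriatric syndromes recorded by patients/or carers", and item (6) is the corresponding incidence of unplanned admissions or emergency care use. The abstract does the same, ending its list of secondary outcomes with "the incidence of unplanned hospital readmission at 6-month follow-up adjusted for baseline value".

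**The concern.** A baseline time level and a baseline covariate make sense for blood pressure, HbA1c, lipids and questionnaire scores, all of which can be measured before discharge. Items (5) and (6) are different: they accumulate after discharge. If no pre-discharge value exists, an analyst who follows the text has nothing to put in the baseline row or the covariate. The choices are then to leave them missing, impute them, enter the same constant for everyone, or depart from the plan. The model form is a second problem. Event counts are bounded at zero and skewed, and their variance moves with their mean; a yes/no outcome has the same mean-variance link.

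These two outcomes carry the trial's safety and health-care-use evidence, and the Discussion gives prevention of readmission as part of the rationale. If the stated model cannot be run, the replacement will be chosen once data exist, which is what a stated model is meant to prevent.

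**Working it through.** **Step 1. Is there a baseline value for items (5) and (6)?**

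| Place in the protocol article | What it says on these events |
|---|---|
| Secondary outcomes, items (5) and (6) | Taken from the patient's intervention diary |
| Stage 1: interventions at hospital, 1.2.1 | The diary is handed out as part of the pre-discharge intervention |
| Usual care | Control patients note the number of events over the 3- and 6-month follow-up in a separate table |
| Data collection | Baseline data are questionnaires plus blood pressure, HbA1c and lipids; no event or admission count is listed |
| Eligibility | Everyone is an inpatient for uncontrolled hypertension or its complications |

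Both recording tools look forward. Current admission status at baseline is the same for all participants, so it could not serve as a covariate: a constant is collinear with the intercept. A covariate missing for everyone would remove all participants from a complete-case fit, or would have to be imputed with no observed values to impute from.

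**Step 2. What if baseline were entered as a constant, such as zero?** The document does not say this would be done; it is one way to force the model to run. Let the 3- and 6-month counts each have variance σ² and correlation r, and ignore ward variation. A participant random intercept implies compound symmetry, so the residual variance is the mean variance minus the mean covariance over the three occasions:

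- mean variance = (0 + σ² + σ²)/3 = 2σ²/3
- mean covariance = (0 + 0 + rσ²)/3 = rσ²/3
- residual variance = σ²(2 − r)/3

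The model variance of the 6-month minus baseline change is twice this per participant, while the true variance is σ². The ratio is 2(2 − r)/3, and its square root is the standard error ratio.

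| r (assumed) | Variance ratio | SE ratio |
|---|---|---|
| 0 | 1.33 | 1.15 |
| 0.5 | 1.00 | 1.00 |
| 0.8 | 0.80 | 0.89 |
| 1 | 0.67 | 0.82 |

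The error can go either way, and it vanishes at r = 0.5. The document gives no r.

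**Step 3. How far are the data from Gaussian?** The document gives no event rate, so the means below are assumptions. For a Poisson count with mean μ per period, the share with no event is exp(−μ), the skewness is 1/√μ, and a normal distribution with the same mean and variance puts Φ(−√μ) of its mass below zero.

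| μ (assumed) | No event | Skewness | Normal mass below 0 |
|---|---|---|---|
| 0.1 | 90% | 3.2 | 38% |
| 0.3 | 74% | 1.8 | 29% |
| 1.0 | 37% | 1.0 | 16% |

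Constant variance fails if the intervention works. In a simulated overdispersed example (control mean 0.3 per period, rate ratio 0.6), the follow-up variance was about 0.35 in control and 0.20 in intervention. Variance at a zero baseline is 0 in both arms.

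**Step 4. Does this reach the primary outcome?** No. Systolic pressure is measured at baseline and is continuous, and the sample size calculation uses that outcome only.

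**The case against.** The strongest reply has four parts.

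- **A baseline count may exist.** The SPIRIT figure, the diary and the usual care table are not shown, and a history of earlier admissions could be collected and would vary between patients. This stands as a limit: a reader might infer that the baseline adjustment is undefined for every participant, but the document supports only that the text describes no such count.
- **Non-normality alone need not spoil a comparison of means.** A simulation of overdispersed counts (assumed means 0.1, 0.3 and 1.0; 5 wards of 25 per arm; between-ward coefficient of variation 0.2 or 0.4), comparing ward means on 8 degrees of freedom, held type I error at 4.7% to 5.1%. This stands for that simple analysis. It does not test the prescribed model, which has a baseline row, a baseline covariate and a common residual variance.
- **Withdrawal need not look favourable.** A reader might infer that someone who leaves early counts as having few events. With recording at 3 and 6 months, a wholly missed period is missing rather than low, and the plan includes withdrawals and provides multiple imputation for large missing data. The worry survives only where a partly observed period is entered as complete.
- **The events may not be rare.** A reader might assume so, but the Discussion calls post-discharge adverse event and readmission rates high. The argument here does not need rarity.

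It might also be said that the model for these outcomes belongs in a statistical analysis plan. That would hold if the article were silent, but it states the model and the baseline adjustment for all secondary outcomes.

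**Conclusion.** The point holds for secondary outcomes (5) and (6) only. The article fixes a linear mixed model with baseline terms for two outcomes that its own text describes solely as follow-up events, so that rule cannot be carried out as written for them. The Gaussian form is also a poor choice whether incidence means a count, which the control arm's recording of a number suggests, or any event.

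No single size can be given. The standard error range of 1.15 to 0.82 times the truth applies only if baseline is entered as a constant and ward variation is ignored, and it includes no error at all at r = 0.5; a reader should not take from it that the variance is necessarily wrong. The Poisson figures rest on assumed rates. The conclusion about the baseline terms rests on the absence of a baseline event count from the text, with the SPIRIT figure and additional files unseen.

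This should be fixed, but it does not threaten the trial's main conclusion: the primary analysis, the sample size and the other four secondary outcomes are outside its reach.

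**What to change.** For outcomes (5) and (6), in the Statistical methods and Secondary outcomes sections and in the abstract:

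1. Remove the baseline adjustment and the baseline time level, and analyse follow-up events only.
2. State whether each outcome is a count or any event.
3. Name a Poisson or negative binomial model for a count, or a logistic model for any event, that accounts for ward clustering.
4. For counts, use a log person-time offset where follow-up or withdrawal dates are recorded. The article does not say that they are, so otherwise use the fixed 3- and 6-month recording periods and say how partly observed periods are handled.
5. Name an inference method suited to 10 wards, for example a comparison of ward-level rates with 10 − 2 = 8 degrees of freedom.
6. If a count of earlier admissions is in fact recorded, it may enter as an ordinary covariate, described as such.

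The cost is wording and standard software, with no change to recruitment or sample size. There is one real downside: the small-sample correction to restricted maximum likelihood that the plan relies on does not carry over to these models, which is why item 5 must be stated explicitly. The change should be documented before outcome data are analysed by group.
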